# Efficacy and safety of piezocision in accelerating maxillary anterior teeth en-masse retraction: study protocol for a randomized controlled trial

**DOI:** 10.1186/s13063-022-06389-4

**Published:** 2022-06-07

**Keywords:** Piezocision, En-masse retraction, Accelerate tooth movement, Orthodontic treatment, Randomized controlled trial/RCT

## Abstract

**Background:**

Orthodontic treatment is commonly more time-consuming in adults than in teenagers, especially when it comes to the maxillary en-masse retraction, which may take 9 months or even longer. As to solve this concern, orthodontists have been striving to seek new methods for shortening orthodontic treatment time. Piezocision, as a popular alternative treatment, has been widely used in different types of tooth movement. However, its effect on en-masse retraction of maxillary anterior teeth remains unclear. This randomized controlled trial intends to figure out the role piezocision plays in accelerating en-masse retraction.

**Methods:**

This protocol is designed for a prospective, single-center, assessor-blinded and parallel-group randomized controlled trial. Twenty adult patients aged from 18 to 40 whose orthodontic treatment required bilateral maxillary first premolars extraction will be randomly assigned to the piezocision group and the control group at a ratio of 1:1. The piezocision group will undergo en-masse retraction immediately after the piezo surgery, while the control group will start en-masse retraction directly. Both groups will be followed up every 2 weeks to maintain the retraction force until the end of space closure. The space closing time is set as the primary endpoint. Meanwhile, the secondary endpoints include the change of root length, labial and palatal alveolar bone thickness, vertical bone height, probing depth of maxillary anterior teeth, cephalometric measurements, visual analogue scale, and postoperative satisfaction questionnaire.

**Discussion:**

This study will attempt to provide more convincing evidence to verify whether piezocision will shorten the time of en-masse retraction or not. Distinguished with previous studies, our study has made some innovations in orthodontic procedure and primary outcome measurement, aiming to clarify the efficacy and safety of piezocision-assisted en-masse retraction in Chinese population.

**Trial registration:**

Chinese Clinical Trial Registry ChiCTR 1900024297. Registered on 5 July 2019

**Supplementary Information:**

The online version contains supplementary material available at 10.1186/s13063-022-06389-4.

## Administrative information

Note: the numbers in curly brackets in this protocol refer to SPIRIT checklist item numbers. The order of the items has been modified to group similar items (see http://www.equator-network.org/reporting-guidelines/spirit-2013-statement-defining-standard-protocol-items-for-clinical-trials/).

## Introduction

### Background and rationale {6a}

To improve facial appearance and oral function, numerous people have an increasing demand for orthodontic treatment [1, 2]. One of the main challenges adult patients and orthodontists face is the prolonged orthodontic treatment time. It may take adults an average of 2–3 years to complete the treatments, depending on the severity of malocclusion and individual characteristics, much longer than the time required for adolescents [3].

The prevalence of convex deformity appeared relatively high in Chinese population. To correct this deformity, the most effective orthodontic treatment is extraction of bilateral maxillary first premolars, following with en-masse retraction (ER) of anterior teeth to improve the facial profile. It might take almost 9 months to retract anterior teeth in cases with upper premolars extraction assisted by miniscrew anchorage [4, 5]. Moreover, various complications, including caries, periodontal diseases, and root resorption, are largely attributed to the prolonged treatment time [6]. Therefore, accelerating orthodontic tooth movement (OTM) to shorten the orthodontic treatment time is currently one of the hottest research focuses.

A large amount of research has been conducted to dig diverse approaches out to accelerate tooth movement during the orthodontic treatment, consisting of surgical and non-surgical interventions generally. Surgical interventions contain corticotomy [7–9], distraction osteogenesis [10–12], and circumferential supracrestal fiberotomy [13–15], while nonsurgical ones include laser [16–21], vibration [22–25], drug [26, 27], ultrasound [28, 29], and electromagnetic therapy [30, 31].

However, non-surgical interventions have problems such as uncertain effects, short effective time, operating inconvenience, and high compliance requirements for patients [32, 33]. On the other hand, surgical interventions are increasingly accepted by both orthodontists and patients. Among them, corticotomy has received extensive attention in recent years [34].

Literature on corticotomy was initially put forward by Kole in 1959, in which corticotomy was used to form free bone blocks to accelerate OTM, resulting in great trauma [35]. Vercellotti and Podesta performed corticotomy with conventional periodontal flap and ultrasound osteotome for accelerating OTM since 2007 [36]. Dibart et al. reported a flapless approach in 2009, which was named after piezocision [8].

The corticotomy with a piezoelectric apparatus is performed after an interdental gingival incision. This method causes much less tissue traumatic damage to patients and accomplishes better prognostic quality, though it takes more time to realize the acceleration of OTM than the conventional flap surgery according to related literatures [37, 38]. However, the total period was shortened by 59% in the experimental group as piezocision was applied to alleviate the crowding of the mandibular dentition [39].

### Objectives {7}

The purpose of this trial is to investigate the efficacy and safety of piezocision in accelerating maxillary anterior teeth ER in normodivergent adults with convex deformity, whose treatment plans involve bilateral maxillary first premolars extraction.

### Trial design {8}

This study will be a single-centered, assessor-blinded, and prospective randomized controlled trial (RCT), which was designed following the guideline of SPIRIT 2013 statement [40]. After initial screening and informed consent forms (ICF) obtained, all subjects will be randomized according to random numbers into the piecocision group (PG) and the control group (CG) in a 1:1 ratio. The observation period of this study will be 12 months. The study design is fully illustrated in the flowchart (Fig. 1).

**Fig. 1 Fig1:**
[figure not shown]
Flow chart of the trial design

## Methods: participants, interventions, and outcomes

### Study setting {9}

All the subjects who are eligible for the trial will be enrolled at Shanghai Stomatological Hospital, from October 2019 to March 2022. Shanghai Stomatological Hospital, as a municipal tertiary hospital, has set the relevant clinical departments of periodontitis and orthodontics, which can meet the demand of this trial. The recruiting announcements will be posted on the official websites of the hospital. In the preliminary trial stage, we have confirmed the scientific validity of piezocision surgical scheme through discussions with several periodontal and orthodontic experts, combined with the results of Dibart et al. [8].

### Eligibility criteria {10}

Participants can only be included in the study if the following criteria are met:

#### Inclusion criteria

Age from 18 to 40, male and femaleGood oral condition: healthy periodontal condition or mild periodontitis (alveolar bone absorption less than 10%), no periapical infection, and unfilled cariesConvex deformity and normodivergent facial pattern with the treatment plan including 2 maxillary first premolars extractionNo or mild overcrowding in maxilla dentition

#### Exclusion criteria

History of temporomandibular disorders, systematic diseases, and systemic metabolic diseasesLaser, radiation workersThe presence of bone island, osteoma, apical cyst, root resorption, and root exposure in the tooth movement areaPeriodontitis patients with alveolar bone absorption more than 10%Gingival recession over 2 mmSmokersAbnormal bone metabolism (including taking anti-bone absorption drugs, hormone drugs, immunosuppressant)Mental disorders or movement disordersPregnancy

### Who will take informed consent? {26a}

A qualified researcher will explain all the details about this trial, including the study procedure, benefits, and potential risks to all the subjects, and ensure that subjects are fully understood. Subsequently, informed consents will be obtained.

### Additional consent provisions for collection and use of participant data and biological specimens {26b}

Since this study will not involve the collection or use of biological specimens, this item is not applicable.

### Interventions

#### Explanation for the choice of comparators {6b}

Considering there is no internationally accepted treatment of accelerating OTM and the intervention in this study is a surgical one, we set the conventional orthodontic group as the control group, aiming to clarify the effectiveness and safety of piezocision on accelerating ER. In order to minimize the bias, participants in both groups will undergo the same orthodontic treatment procedure, operated by one senior orthodontist.

#### Intervention description {11a}

Following randomization, all the participants will receive straight wire orthodontic treatment utilizing self-ligating brackets (H20, Jinhua, Zhejiang, China) with the slot size of 0.020×0.028 inches. The maxillary dental arch will be aligned and leveled utilizing nickel-titanium wires in the following order: 0.014niti, 0.018niti, 0.014×025niti, and 0.018×025niti, with a senior orthodontist evaluating whether the alignment and leveling have been fully achieved. Subsequently, elastics with a force of 250 g per side will be applied to the traction hook on the distal side of the lateral incisor brackets, which is 8 mm long, with orthodontic anchorage provided by mini-screws implanted in the zygomatic alveolar crest area. Before beginning ER, the 0.018×025 stainless-steel wire should be left in place for 4 weeks to guarantee minimal sliding resistance.

The participants will have either piezo-assisted ER or conventional ER. Prior to retraction, patients in PG will get piezo surgery. Afterwards, all the participants must be revisited every 2 weeks to replace the elastics in order to maintain the retraction force until the space is completely closed. The piezocision operation will only be performed by a senior periodontist with clinical experience more than 10 years. Meanwhile, a chief orthodontist will be responsible for orthodontic treatment and mini-screws placement in the zygomatic alveolar ridge. Preceding the trial, all researchers will get training in accordance with the protocol. Subjects’ enrollment and assignment, standard treatment procedure, case report forms (CRF) filling, and adverse event reporting system (AERS) will be all elaborated in the training conference.

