### Implementation {16c}

An independent researcher will be responsible for the enrollment of participants. After signing the ICF and screening, eligible subjects will receive SNOSE with orderly numbers according to the order of enrollment. The investigator will write down the patients’ detailed information (name, gender, age, and ID number) on the SNOSE and take out the cards immediately. The subjects’ group will be determined by the random numbers in the SNOSE. The random operator and the random date will be recorded.

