## Assignment of interventions: blinding

### Who will be blinded? {17a}

Since the intervention in this RCT is a surgery treatment and setting a sham surgery may cause unnecessary harm to the participants, the medical staff and subjects cannot be blinded in this study. To minimize the bias, the outcome assessor and data statistical analyst will be blinded during the trial.

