## Data collection and management

### Plans for assessment and collection of outcomes {18a}

After randomization, participants in PG will undergo ER immediately after piezocision surgery, while the ones in CG will receive ER therapy directly. All of them will be asked to fill out the VAS for 7 successive days after ER to compare the discomfort feeling between the two groups. Subjects in PG will additionally fill in the PSQ after the surgery.

The primary outcome is the space closing time (T_V2-V1_), which will be measured from the initiation of ER (V1) till the end of the space closure (V2).CBCT will be taken at V0 and V2 to measure the root length and the thickness of the labial and palatal bone of the 6 maxillary anterior teeth. Dolphin will be used for cephalometric analysis of lateral radiographs to analyze indexes related to dental, skeletal, and soft tissue changes including U1-SN, SNA, MP-SN, and UL-E.

Study staff, including orthodontists, periodontists, clinical study nurses, CRC, assessors, and statisticians, will be trained in data management.

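### Allocation is revealed at enrolment, before an alignment phase common to both arms, so knowledge of the arm can affect the patient's state at V1 and who reaches V1

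*Protocol article*

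**What the plan says.** All references are to the protocol article.

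- *Implementation {16c}*: once consent and screening are done, "The investigator will write down the patients’ detailed information (name, gender, age, and ID number) on the SNOSE and take out the cards immediately". *Outcome measures {12}* places V0 before randomisation and V1 at the start of en-masse retraction (ER).
- *Intervention description {11a}*: "Following randomization, all the participants will receive straight wire orthodontic treatment utilizing self-ligating brackets". Four nickel-titanium wires follow, "with a senior orthodontist evaluating whether the alignment and leveling have been fully achieved". Then: "Before beginning ER, the 0.018×025 stainless-steel wire should be left in place for 4 weeks to guarantee minimal sliding resistance".
- The arms part only after this: "Prior to retraction, patients in PG will get piezo surgery". The control group starts retraction without surgery.
- *Primary outcome*: the endpoint is the time from V1 to closure (V2). A blinded assessor logs the visits and judges closure with dental floss.
- *Who will be blinded? {17a}*: "the medical staff and subjects cannot be blinded in this study".
- *Statistical methods {20a}*: the full analysis set needs at least one treatment after randomisation and a corresponding evaluation. Section {20c} assigns 12 months to anyone who drops out or is still unclosed at 12 months.

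**The concern.** Between opening the envelope and V1, every patient goes through bonding, alignment, levelling, mini-screw placement and four weeks on steel wire, the same in both arms. The protocol gives no reason for fixing the allocation before this phase. Two things are at stake.

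**State at V1.** Medical staff know the arm, and one of them decides when alignment is complete. No criterion is stated, and the blinded assessor is not said to have any part in that decision. If the decision leans differently by arm, residual space or tooth position at V1 can differ by arm, and the closing time inherits the difference. Blinding the judgement of V2 does not protect V1.

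**Who reaches V1.** Patients may leave during alignment, or decline a surgery they have known about since enrolment, before the treatments have differed at all. They have no V1 and so no primary interval. The full analysis set definition and the 12-month rule do not settle whether they are excluded or counted as 12 months. With 10 patients per arm, one or two of them matter.

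**Working it through.** **1. Inputs.** From *Sample size {14}*: control mean 9 months, piezocision mean 5.4 months, SD 2, significance level 0.05, 90% power, 20% dropout, 10 per arm. From *Statistical methods {20a}*: t test or Mann-Whitney test, two-sided. From {20c}: 12 months for dropouts and for patients unclosed at 12 months. Not given: the number lost before V1 and the length of alignment. The loss counts below are assumptions.

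**2. The protocol's own figure.** Standardised difference = (9 − 5.4)/2 = 1.8. A two-sided t test at 0.05 with 90% power needs 7.59, so 8 per group (actual power 91.7%). 8/(1 − 0.20) = 10 per group, 20 in total. The stated sample size reproduces and is not disputed.

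**3. Means after the 12-month cap, no losses.** Control: 9 − 2 × [φ(1.5) − 1.5 × (1 − Φ(1.5))] = 9 − 2 × (0.1295 − 1.5 × 0.0668) = 8.94. Piezocision: the cap lies (12 − 5.4)/2 = 3.3 SD above the mean, so the mean stays 5.40. Difference = 3.54 months.

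**4. Mean difference when patients lost before V1 are given 12 months.**
- 2 lost in each arm: 0.8 × 3.54 = 2.8 months.
- 2 lost in piezocision, 0 in control: 8.94 − (0.8 × 5.40 + 0.2 × 12) = 8.94 − 6.72 = 2.2 months.
- 0 lost in piezocision, 2 in control: (0.8 × 8.94 + 0.2 × 12) − 5.40 = 9.55 − 5.40 = 4.2 months.
- No true effect, 2 versus 0: 0.2 × (12 − 8.94) = 0.6 month, purely from the imbalance.

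**5. Power.** Simulation, 100,000 runs, t test, 10 randomised per arm, values capped at 12 months:

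| Lost before V1 (piezocision / control) | Power if excluded | Power if given 12 months | Difference if given 12 months |
|---|---|---|---|
| 0 / 0 | 97% | 97% | 3.5 |
| 1 / 1 | 95% | 85% | 3.2 |
| 2 / 2 | 92% | 62% | 2.8 |
| 3 / 3 | 87% | 34% | 2.5 |
| 2 / 0 | 95% | 35% | 2.2 |
| 0 / 2 | 95% | 99% | 4.2 |

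With no true effect, a 2-versus-0 imbalance given 12 months is rejected in about 8% of runs instead of 5%. The 2 / 2 row puts the whole planned 20% dropout before V1; the 1 / 1 row puts half of it there.

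**6. The V1 judgement.** No arithmetic applies, because the protocol gives nothing from which to size a difference in patient state at V1.

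**The case against.** The case for the protocol as written is substantial.

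- The endpoint is counted from V1, so an earlier or later V1 does not by itself shorten or lengthen it. Bias needs a difference in the patient's condition at V1. This stands, and it limits the claim.
- Discretion is narrowed. Entry requires no or mild maxillary crowding, one senior orthodontist treats both arms by the same procedure, the wire sequence and the four weeks on steel wire are fixed, and closure is judged blind. This stands too, but the four weeks follow an alignment phase whose end is judged with the arm known, so the path is narrowed and not closed.
- The large power losses come from the 12-month fill. If the same patients are excluded, one or two losses per arm leave 95% to 92%. That is correct. However, later randomisation removes these patients from the comparison however missing data are handled.
- The pre-V1 loss is assumed. The 20% dropout is not split by phase.

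Two stronger readings are tempting, and neither is supported. A reader might infer that *Plans for assessment {18a}* contradicts {11a}, because it says "After randomization, participants in PG will undergo ER immediately after piezocision surgery, while the ones in CG will receive ER therapy directly". There, the immediacy links surgery to retraction. The sentence leaves out the alignment phase but does not move randomisation. A reader might also infer that 12 months run from randomisation, because "The observation period of this study will be 12 months" comes right after the randomisation sentence, so that most controls could not finish. No starting point is given there. Section {20c} uses 12 months as a value of the V1-to-V2 interval, and the Discussion uses observation time for the retraction period.

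**Conclusion.** The point holds as a design weakness that should be fixed, with moderate confidence. Early open allocation, an allocation-aware readiness judgement without a stated criterion, and unclear handling of patients who never reach V1 are all in the text. Together they allow the arm to affect the state at V1 and who contributes to the primary comparison.

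The effect through the V1 judgement cannot be sized from the document. The effect through losses depends on an assumed count and on 12 months being applied to patients who never started ER. On those assumptions, two losses per arm reduce power from about 97% to 62%, and a one-sided loss of two moves the estimate to 2.2 or 4.2 months, against 3.5 without loss. Under exclusion the cost in power is small.

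**What to change.** Keep consent, screening and V0 as they are. Open the sealed envelope only after the orthodontist has signed off readiness for ER at the end of the stainless-steel phase. Before opening, reserve the ER start date or surgical slot for every patient, so that V1 is not delayed in the piezocision group alone. Amend *Intervention description {11a}* and *Implementation {16c}*, and the order of events in *Trial design {8}* and *Plans for assessment {18a}*. In {8}, state that the 12-month observation period runs from V1.

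*Trial status* says recruitment began in October 2019, so some patients may already be randomised under the present order. For them, have readiness recorded by someone blinded to the arm, such as the existing assessor. Do not assign 12 months to patients who never started ER; report them by arm.

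Cost: no extra visits or staff. Some consented patients will never be randomised, and slots must be reserved provisionally. The target of 20 randomised is unchanged. With all 10 per arm reaching V1, power is about 97%, less any loss during ER.

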##### Piezocision group (PG)

Piezocision will be performed in 4 weeks after the placement of 0.018×0.025-in. stainless steel archwire and insertion of mini-screws. The patient will be anesthetized with local infiltration (Articaine 4% with 100,000 epinephrine) after a 1-min flush with chlorhexidine gluconate 0.12%. The surgical procedure will be performed as described by Dibart et al. [8]. Once anesthesia has set, vertical incisions will be performed in the attached gingiva of maxillary anterior region buccally and interproximally using a scalpel with a blade No. 15. Incisions will be started 4 mm below the base of the interproximal papillae to prevent any further gingival recessions. A piezo surgical knife (Satelec, Acteongroupe, Merignac, France) will be used to create the cut. The vertical length will be 5–8 mm and the depth of the cut will be approximately 3 mm. The incisions will not be sutured. Patients will be required to avoid hot and spicy food for 5–7 days and maintain oral hygiene after surgery.

The elastic chain will be extended bilaterally from the mini-screws to the power hooks to initiate the ER immediately following the surgery. In order to confirm the force (250 g), a dynamometer (Xihu Cooperation, Hangzhou, China) will be used (Fig. 2).

**Fig. 2 Fig2:**
[figure not shown]
The ER treatment after the piezocision surgery

##### Control group (CG)

This group of patients will only undergo orthodontic therapy. The elastic chain will be stretched from the screws’ head to the power hooks for ER.

#### Criteria for discontinuing or modifying allocated interventions {11b}

Subjects who are unable to complete follow-up for any reason can quit the study at any time without consequences. Participants can drop out of the trial if they have any of the following behaviors that affect outcomes during the trial, including smoking, pregnancy, and taking medications that may affect bone metabolism. Furthermore, if adverse events (AE) occur during treatment, the subjects will be allowed to discontinue the study. We will document a detailed record of the procedures.

